## Abstract

We designed a controlled trial protocol that seeks to contribute to cognitive science by studying the effect of thought training on children's executive functions. The study design is a cluster randomized controlled trial, with intra-subject and inter-subject evaluation, with two parallel groups: an experimental group and a TAU control group. With three measures, pre-test, post-test, and follow-up after three months. The participants will be children aged 9 to 11. The allocation will be randomized by groups and not individually. The sample will be a minimum of 44 participants. The primary measures will be neuropsychological tests to assess executive functions. Secondary measures will be a computational thinking test, neuropsychological tests to assess metacognition and attention, and an acceptability scale. The experimental group will participate in the COGNI-MACHINE computational thinking training designed by the first author. The training frequency will be twice a week in 60 min sessions for 12 weeks. The TAU control group will receive computer science classes as usual during the same time as the experimental group. The evaluators taking the measurements will be blinded to the assignment. The investigators in charge of the intervention will be blinded to the results of the evaluations.

Specifications table

**Table utbl0001:** 

Subject Area:	• Cognitive sciences
More specific subject area:	• Children's Cognitive Development
Protocol name:	Effect of COGNI-MACHINE computational thinking training on executive functions in children aged 9 to 11: Protocol of a Cluster Randomized Controlled Trial
Reagents/tools:	• Cogni-Machine computational thinking training • Micro:bit based robotics kit • Code.org courses
Experimental design:	The protocol has a Cluster Randomized Controlled Trial design, with intra-subject and inter-subject evaluation, with two parallel groups: experimental and TAU control groups. With three measures, pre-test, post-test, and follow-up after three months. The participants will be four fifth-grade courses, aged 9 to 11. The allocation will be randomized by groups and not individually. The final sample will be a minimum of 44 participants. The primary measures will be neuropsychological tests to assess executive functions (cognitive flexibility, working memory, inhibitory control, and planning). Secondary measures will be a computational thinking test, neuropsychological tests to assess metacognition and attention, a sociodemographic questionnaire, and a satisfaction and adherence scale. The experimental group will participate in the COGNI-MACHINE computational thinking training designed by the first author. The intervention will occur at the educational institution twice a week in 60-minute sessions lasting 12 weeks and 24 sessions. The TAU control group will receive their computer science and technology classes as usual simultaneously and with the same hourly intensity. The evaluators taking the pre-test and post-test measurements will be blinded to the assignment. Moreover, the researchers in charge of the intervention will be blinded to the results of the evaluations.
Trial registration:	The study protocol was registered in International Standard Randomized Controlled Trial Number – ISRCTN, with registration number ISRCTN11380198.
Ethics:	The study protocol was submitted to the Research Ethics Committee of Universidad del Tolima and approved under act No.10 of December 13, 2022.
*Value of the Protocol:	• This protocol is important to verify the effects of COGNI-MACHINE computational thinking training on the development of executive functions of children in the last years of the primary school cycle. • There are some previous studies on the effects of computational thinking on executive functioning in children; however, this is a field of study that requires further development. • The novelty of the COGNI-MACHINE training, compared to other training, is that it seeks to take advantage of the use of unplugged and plugged activities in computational thinking, as well as incorporate educational robotics through project-based learning.

## Introduction

Executive functions (EF) constitute a series of high-level cognitive processes regulating thought, action, and emotion underlie flexible goal-directed responses to new or difficult situations [1], [2], [3]. These cognitive processes depend mainly on the prefrontal areas of the cerebral cortex and their links with other subcortical areas [4] related to the temporal organization of behavior [5]. The prefrontal cortex has a slow and progressive evolution that begins in childhood and reaches its peak in adulthood [[6], [7], [8], [9]]. This means that the development of executive functions is highly dependent on stimulation throughout the development of the subject and that the first years of life are a critical period for acquiring the basic elements that will enhance executive functions throughout life childhood and adolescence [[1], [10], [11], [12]].

The academic community has studied different intervention approaches for executive functions, such as curricular approaches [[13], [14]], programs based on physical activity ([[15], [16]], traditional cognitive training [[17], [18], [19]], cognitive behavioral therapies [[20], [21]], music therapy [22], interventions based on digital technologies [23], [24], [25], [26] , neurofeedback [27], transcranial direct current stimulation [[28], [29]].

In their systematic review, Robledo-Castro et al. [30] compiled studies that evaluated interventions to stimulate executive functions based on computer systems. Among these interventions aimed at children, serious games can be distinguished [[31], [32]], some commercial video games [[33], [34]], programs based on classic tasks [[35], [36]]; interventions that incorporated virtual reality technology [37], among others. The authors also found that research on computational thinking training is another area of study that has shown different effects of teaching coding and programming on children's executive functions [[38], [39], [40], [41], [42], [43], [44], [45], [46], [47], [48], [49], [50], [51]].

Computational thinking refers to a particular way of reasoning to solve problems efficiently following the principles of computational sciences [[52], [53]]. It is a set of cognitive processes involved in a particular approach to interpret, analyze and solve problems [54], which includes: the ability to analyze the problem space, reduce the difficulty of the problem by breaking it down into smaller units, express and represent the solution through algorithms or sequences of instructions, and, finally, correct the execution and verify the scope of the objective [[55], [56], [57], [58]].

One of the tools to develop computational thinking is teaching programming or coding [59]. Knowing the effects of teaching programming and coding on higher cognitive functions has been another line of study that had its first approaches with authors such as Pea & Kurland [60], with variable results. You can also find the meta-analyses [[61], [62], [63]], which jointly compiled 192 studies and evaluated more than a thousand transfer effects of programming learning in different cognitive processes. These meta-analyses concluded that teaching coding and programming at school ages improves computer skills and other higher-order cognitive processes such as critical thinking, mathematical thinking, creative thinking and metacognition, spatial skills, and reasoning.

In recent years, some studies have evaluated the effects of teaching computational thinking on executive functions in childhood. Some of these studies have found small to large effects on executive functions such as planning, inhibitory control, goal-directed behavior, visuospatial working memory, and other cognitive processes such as sequencing, fluid intelligence, problem-solving, verbal and nonverbal reasoning., mathematical skills, reflective thinking, and creative thinking [[38], [39], [43], [45], [46], [49], [50], [64], [65]].

Even though there are some studies on the subject, these are still scarce, and all the authors conclude on the need to strengthen and expand this field of study to provide feedback to existing intervention programs and impact on public and educational policies [46]. Studying the effects of teaching computational thinking on executive functions and other cognitive processes will allow knowing the impact of study plans and programs aimed at teaching computational thinking, recognizing the most appropriate type of activities concerning the ages of the students and their level of development, the real scope of these initiatives and their differential effect in different periods of cognitive development and different executive functions.

### Specific objectives and hypotheses

The following randomized controlled trial (RCT) protocol was designed to evaluate the effect of the COGNI-MACHINE computational thinking training program on the executive functions of fifth-grade children aged 9 to 11 years. This RCT has established the following working hypothesis:

There are significant differences in the evolution of executive functions and other cognitive processes, such as metacognition and attention, in fifth-grade children who receive training in computational thinking compared to those children who receive a conventional computer training program.

## Method

### Protocol design

A randomized controlled trial will be conducted by groups, with intra-subject and inter-subject evaluation, with two parallel groups, one experimental and the other in active control with treatment as usual. Three measures will be applied: pre-test, post-test, and follow-up at three months. The clinical trial protocol has been designed following the guidelines of the CONSORT Statement [66]. The trial has been registered in the International Standard Randomized Controlled Trial Number - ISRCTN, a primary clinical trial registry recognized by the World Health Organization, with registration number ISRCTN11380198 and can be consulted at: https://www.isrctn.com/ISRCTN11380198. Fig. 1 shows the layout of the experimental design.

**Fig. 1 fig0001:**
[figure not shown]
Layout of the experimental design. *Note:* RG1: Experimental group; RG2: Control group; On: Measure; X: Intervention.

For the intra-subject analysis, each group will be evaluated before starting the intervention (T1) and after the intervention (T2). Three months after the end of the intervention, a third follow-up measure (T3) will be applied to the experimental group to recognize the permanence of the effect over time. Once the post-test phase is over, the control group will receive the same training in computational thinking. For the intersubject analysis, the study will include an active control group in treatment as usual (Treatment-As-Usual - TAU), which consists of receiving the usual treatment in parallel to the experimental group and for the same time as the experimental group [[67], [68]].

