### Interventions

#### Experimental group

The experimental group will participate in a training in computational thinking called COGNI-MACHINE, designed by the first author. The intervention comprises 24 sessions; each session will be structured as a workshop and will take place in the computer room of the participating educational institution. The intervention will last 12 weeks, with two sessions per week of 60 min each.

The training workshops will be based on the principles of problem-based learning, and the activities will be designed following the principles of low floor / high ceiling. For the design of the computational thinking intervention, the following sources were taken into account: (1) The recommendations emerging from the results of the previously conducted pilot test [[30], [45]]; (2) A broad review of activities, projects, and courses available to teach computational thinking in school contexts; (3) A systematic review of background and similar studies.

To select the plugged and unplugged activities that would be part of the training, we reviewed: (1) Existing open-access training and existing repositories of unplugged activities; (2) The integrated development environments available to learn to code in blocks; 3) The educational robotics devices available in the market for Colombia. From these reviews, unplugged activities were selected from different sources such as CS Unplugged, code.org, programemos.com, and Mintic's “Coding for kids” [88]. Lessons from courses B, C, and D of the code.org integrated development platform and the Makecode integrated development platform were selected for the block programming activities. For the plugged projects, he selected the micro:bit V2 microprocessor (see Fig. 2), which is a small programmable board designed by the BBC which has several integrated sensors, Bluetooth connection, radio frequency, push buttons, and LED light outputs.

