#### Control group

The control group at TAU will receive the traditional Technology and Computer Science classes 2 hours a week for 12 weeks. In these classes, students will learn to use Microsoft Office applications. After the 12 weeks of intervention, a crossover design will be conducted so that the control group participates in the same intervention as the experimental group and the experimental group participates in the 12 weeks of traditional technology classes.

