### Statistical analysis plan

A hypothesis test will be conducted through Mixed Repeated Measures Analysis of Variance (ANOVA MR) with Bonferroni corrections to look at the differences between groups, in which the pre-test, post-test, and follow-up measures will be the factor of repeated measures. (Within-subject) and the difference between the experimental and control groups as the subject factor. The effect size will be measured with partial eta squared. The assumptions of this type of analysis assume a continuous metric-dependent variable with approximately normal distribution and with homoscedasticity in each of the groups.

A multivariate linear regression analysis will also be performed to assess the correlations between cognitive measures and computational thinking. And logistic regressions to analyze binary variables to evaluate the association between the covariates and the results.

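### The three-month measure has no untrained comparator and, as described, goes to the experimental arm, so the planned two-arm, three-time-point ANOVA and the permanence claim do not hold; the pre-test to post-test comparison does.

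*Protocol article*

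**What the plan says.** All references are to the protocol article.

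- **Who is measured when.** Protocol design opens with a general statement: "Three measures will be applied: pre-test, post-test, and follow-up at three months". It does not limit the third measure to one arm. The text under Fig. 1 is more specific. For T1 and T2, "each group will be evaluated before starting the intervention (T1) and after the intervention (T2". For T3, "a third follow-up measure (T3) will be applied to the experimental group to recognize the permanence of the effect over time".
- **What controls receive next.** The same paragraph says "Once the post-test phase is over, the control group will receive the same training in computational thinking". The Control group section agrees: "a crossover design will be conducted so that the control group participates in the same intervention as the experimental group". The experimental children move to the usual technology classes for those 12 weeks.
- **How long the training takes.** The Experimental group section says "The intervention will last 12 weeks, with two sessions per week of 60 min each".
- **How the data are analysed.** The Statistical analysis plan section specifies a mixed repeated-measures ANOVA "in which the pre-test, post-test, and follow-up measures will be the factor of repeated measures", with experimental versus control as the between-subject factor.
- **How the trial is sized.** Table 2 lists two groups, three measures, alpha 0.05, power 0.95, an effect size of 0.25 to 0.5, and 44 children.

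Nowhere does the article state a T3 for controls, limit the between-arm test to T1 and T2, or give T3 an analysis of its own.

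**The concern.** The schedule and the analysis describe different designs. The analysis and the sample size need a T3 value in both arms. The schedule names each group for T1 and T2, then only the experimental group for T3, and it trains the controls in the interval. No arm is left untrained at three months.

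Two things are at stake. The only between-arm test that the article specifies either cannot be run as written or includes a time point that no longer contrasts training with usual classes. And the stated purpose of T3, to show that the effect lasts, has no comparator. If this is settled only after the data are seen, dropping T3 from the main test becomes an unplanned change to that test.

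**Working it through.** **1. The design as a table**

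| Arm | T1 | T2 | T2 to T3 | T3 |
|---|---|---|---|---|
| Experimental | measured | measured after training | usual classes | measured |
| Control | measured | measured after usual classes | same training, 12 weeks | not named in the schedule |

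Three months is about 13 weeks and the controls' training lasts 12. On the stated schedule they have completed or nearly completed it by T3. Exactly how far they have got depends on the length of post-testing and on the school calendar, neither of which is given.

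**2. Reading (a): controls have no T3.** The control-by-T3 cell is empty, so the two-by-three interaction (2 numerator df) cannot be estimated. A repeated-measures ANOVA that needs all three values drops every control child. The imputation in Table 3 does not help. It is tied to children excluded for attending under 70% of the training, and there would be no control T3 data to impute from.

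**3. Reading (b): controls are tested at T3.** The T3 contrast is then earlier versus recent training. The hypothesis in Specific objectives and hypotheses contrasts trained children with children in a conventional computer programme, and T3 does not address it. The T1-T2 contrast is untouched.

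**4. Permanence, under either reading.** The T2-to-T3 change in the experimental arm adds together retention, three months of maturation in children aged 9 to 11, a third exposure to the same tests, and ordinary schooling. Without an untrained group at T3 these cannot be separated.

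**5. The plan's own sample size.** For the within-between interaction with k groups, m measures and N children: λ = f²·N·m/(1−ρ), df1 = (k−1)(m−1), df2 = (N−k)(m−1).

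- From Table 2: k = 2, m = 3, alpha 0.05, N = 44.
- Assumed: the effect size is Cohen's f at its lower end, 0.25 (no metric is named); correlation ρ = 0.5; sphericity.
- λ = 0.0625 × 44 × 3/0.5 = 16.5, df 2 and 84, power 0.956. At N = 42 power is 0.946, so 44 is the smallest even total that reaches 0.95.

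The stated 44 is reproduced with three measures. The within-factor test gives the same N; the between-factor test would need 142.

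**6. The same test on T1 and T2 only (m = 2).** λ = 0.0625 × 44 × 2/0.5 = 11, df 1 and 42, power 0.900.

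| Assumed ρ | Power at N = 44 | N for power 0.95 |
|---|---|---|
| 0.3 | 0.78 | 76 |
| 0.5 | 0.90 | 54 |
| 0.7 | 0.99 | 34 |

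At f = 0.5, power at N = 44 exceeds 0.999 for all three correlations.

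**7. T2 adjusted for T1.** With two measures, f = 0.25 means a between-arm difference in change of 1 SD (f = difference/4). Adjusting for T1 divides λ by 1−ρ² where the change score divides by 2(1−ρ). At ρ = 0.5 this gives λ = (44/4)/(1−0.25) = 11/0.75 = 14.7, df 1 and 41, power 0.962.

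**8. How much reading (b) costs the three-level test.** Take a 1 SD difference at T2 that vanishes at T3. The difference profile is (0, 1, 0), with deviations from its mean of (−1/3, 2/3, −1/3). Each arm carries half, so f² = (1/4) × (6/9)/3 = 1/18. Then λ = (1/18) × 44 × 3/0.5 = 14.7, df 2 and 84, power 0.93.

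Steps 5 to 8 ignore clustering, as the reproduced figure does.

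**The case against.** **The wording on T3 does not exclude controls.** The schedule never says that only the experimental arm is tested, and Fig. 1, which may mark measures by arm, is not shown here. This stands as a caution. The move from each group to the experimental group within one paragraph still supports the one-arm reading, and if T3 is meant for both arms the problem becomes reading (b).

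**Under reading (b) the analysis does not collapse.** This stands. A reader might infer that the trial then has no usable primary comparison. The documents do not support that: T1 and T2 precede the swap, a difference at T2 still drives the interaction (power 0.93 even with full convergence at T3), and the planned Bonferroni-corrected comparisons can isolate T2. What fails is reading T3 as training versus usual classes.

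**The power loss is slight.** This also stands. The fall to 0.90 depends on an assumed f and correlation, and adjusting for T1 removes it under the same assumptions. Recruitment also expects about 100 children, with 44 as a minimum. The two-measure interaction test gives 0.985 at 70 children and 0.999 at 100, again before clustering.

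**Permanence is a within-arm aim and not part of the stated hypothesis.** True, but it is the declared purpose of T3, and a within-arm change cannot show it.

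**Blinding at T3.** A reader might infer that assessors cannot be blind at a visit that one arm attends. The documents do not establish this. The specifications table limits its blinding statement to pre-test and post-test, the Abstract and Table 3 are worded more generally, and nothing says that the outside evaluator would know which arms attend.

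**Conclusion.** The point holds. The schedule gives T3 to the experimental arm, while the analysis and the sample size treat it as a two-arm measure. As written, the three-level group-by-time test either has an empty control cell or includes controls who have completed or nearly completed the training. Neither version supports a claim that the effect is permanent.

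The damage is confined to T3. The randomised T1-T2 comparison remains valid, and the power consequence is small or nil: about 0.90 for the two-measure interaction, or about 0.96 with adjustment for T1, against 0.956 for the three-measure basis at 44 children. These figures assume f = 0.25, ρ = 0.5 and no clustering, with sphericity for the three-measure figure; for the two-measure interaction the range is 0.78 to 0.99 over ρ from 0.3 to 0.7. It would go too far to say that the trial has lost its control arm, or that controls are certain to have finished training by T3.

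**What to change.** 1. State which arms are measured at T3, and make Protocol design, Table 2, the Control group section and the Statistical analysis plan agree.
2. Define the randomised between-arm test on T1 and T2 only. Either the group-by-time interaction restricted to those two measures or T2 adjusted for T1 will do; name one in advance.
3. Report T3 as a descriptive, uncontrolled estimate within the experimental arm, with a confidence interval. Replace the permanence wording with a statement of score level three months after training without a concurrent control. If controls are also tested, label that contrast as earlier versus recent training.
4. Restate the sample-size basis with two measures, giving the effect-size metric and the assumed correlation.

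The cost is wording and analysis specification; no change to the intervention or the visits is needed. The price is that the trial makes no causal claim about durability.

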### Inclusion and exclusion criteria

This study will include children in fifth grade of primary school between 9 and 11 years old. Table 1 contains the criteria for including data from children in the controlled trial.

**Table 1 tbl0001:** Inclusion and exclusion criteria.

Inclusion criteria	Exclusion criteria
1. Children of both sexes.	1. Children with uncorrected sensory impairment.
2. Children who at the time of the beginning the study are between 9 and 11 years old.	2. Children with a psychiatric diagnosis.
3. Children enrolled in fifth grade of primary school in an educational institution of Ibagué, Colombia.	3. Children who exceed the age range at the beginning of the pre-test.
4. Children with typical cognitive development.	4. Children with previous experience in computational thinking, coding or programming training.
5. Children who have participated in 70% of the intervention.	5. Children who have joined the educational institution after the application of the pretest.

